### Survey timepoints

To begin the trial, we will conduct a 40-minute assessment of patients in the YPT and UC conditions to measure their demographic and clinical characteristics, any socioeconomic barriers to transplant, as well as their baseline DDKT and LDKT knowledge, decision-making, readiness, and self-efficacy. Upon beginning evaluation approximately 3–5 weeks later, patients in the YPT condition will repeat components of the survey during a 10-minute assessment. Four and 8 months later, patients in both conditions will complete two more 15-minute surveys to assess how their knowledge, decision-making, and behavior are changing over time. During the final 8-month interview, we also will ask patients questions regarding the cultural competency of their medical providers and other process measures including whether they had made an informed decision as to whether or not pursue DDKT or LDKT, and the overall helpfulness of the education they received.

For patients in the UC education condition, no additional education or coaching will occur after these surveys are administered. Patients in the UC education condition will receive a $10 gift card and a letter of thanks in the mail after each time point. Patients in the YPT condition will receive additional education and tailored coaching, as discussed next.

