### Power and sample size

The sample size and power calculation for this trial was treated as a test of the proportional differences between YPT and UC patients in the Action stage of LDKT readiness at 8-months post-baseline. Based on previous work, we conservatively estimated that, at 8 months post-baseline, 10% of UC patients and 20% of patients in YPT group would reach the Action stage [10, 33]. Assuming a one-tailed alpha of 0.05, a sample size of 300 patients per group is required at 8 months post-baseline to achieve power of 0.80 (total n = 600). Assuming an 8-month post-baseline retention rate of 66%, a total sample size of 450 per education condition will need to be recruited/consented at baseline (n = 900). This sample size will provide sufficient sensitivity to detect a difference in increase in LDKT readiness (i.e., moving to Action) of about 10% between treatment (YPT) and control (UC) groups using logistic regression.

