### Statistical analyses

All statistical tests will employ an intent-to-treat (ITT) approach wherein subjects will maintain their assignment to the treatment condition to which they were originally randomized regardless of whether they actually end-up receiving the planned interventions or not [56]. Multiple imputation of missing data will be used for the analyses [57]. The alpha level for all tests will be set at 0.05, and random effects models will be used to account for longitudinal measurement and linear regression employed for normally distributed outcomes, logistic regression for binomially distributed outcomes, and Poisson regression for count outcomes. The social, demographic, and other characteristics of patients who refuse to join the study or are never successfully contacted will be compared to those who do not to determine if the patient selection procedure has resulted in a biased sample. A similar analysis will be conducted to compare the patients who drop-out of the study to those who do not to determine if patient attrition has biased the sample.

To test whether, compared to the UC education condition, Black, Hispanic, and White patients receiving YPT increase in their LDKT readiness, we will first examine the proportion of individuals moving into the Action stage for readiness to accept a LDKT 8 months post-baseline between the YPT and UC conditions. For a more fine grained assessment of change in LDKT and DDKT readiness throughout the study, change by three occasions (baseline, 4 months post-baseline, and 8 months post-baseline) will be examined. To assess differences in transplant knowledge, DDKT/LDKT self-efficacy, and DDKT/LDKT decisional balance, comparisons between the YPT and UC conditions by these three occasions will be made to determine if the intervention increases transplant knowledge, DDKT/LDKT self-efficacy, and DDKT/LDKT decisional balance scales. Finally, differences in the number of small steps toward LDKT and DDKT will be examined at these three time points.

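### The 8-month LDKT readiness outcome is worded both as being in Action and as moving into Action, and the counting of patients already in Action at baseline is not fixed

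*Protocol article*

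**What the plan says.** All references are to the protocol article.

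- **Power and sample size** opens by treating the calculation as a test of "proportional differences between YPT and UC patients in the Action stage of LDKT readiness at 8-months post-baseline". That is a status at one time point.
- The same section then assumes that "10% of UC patients and 20% of patients in YPT group would reach the Action stage" and ends by saying that the sample can "detect a difference in increase in LDKT readiness (i.e., moving to Action) of about 10% between treatment (YPT) and control (UC) groups". Both describe a transition.
- **Statistical analyses** says "we will first examine the proportion of individuals moving into the Action stage for readiness to accept a LDKT 8 months post-baseline", again a transition.
- **Outcome measures** defines LDKT Action by self-report, as currently taking steps to pursue LDKT. It is the highest of the four LDKT stages listed.
- **Survey timepoints** states that both arms are assessed at the outset for "baseline DDKT and LDKT knowledge, decision-making, readiness, and self-efficacy", so baseline stage is known for everyone surveyed.
- **Patient recruitment, eligibility, randomization, and retention** has two inclusion and six exclusion criteria. None refers to readiness stage.

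The article does not say whether patients in LDKT Action at baseline are left out, counted as non-movers or counted as successes. It names no baseline-stage covariate for the 8-month comparison. A separate analysis of readiness over baseline, 4 and 8 months is planned.

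**The concern.** Being in Action at 8 months and moving into Action by 8 months are the same outcome only when the baseline share in Action is zero. Nothing in the eligibility criteria makes it zero. Table 2 also plans brochures for patients in Preparation or Action at the evaluation visit, 3 to 5 weeks after baseline, so some patients are expected in Action early.

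The definition decides who is in the denominator, who counts as an event, and what the assumed 10% and 20% mean. If it stays open, the outcome that sizes the trial can be read in at least three ways, and the choice among them could be made after the data are seen. Excluding baseline-Action patients also needs to be squared with the intent-to-treat statement.

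**Working it through.** **Inputs.** From the power section: 10% (UC) versus 20% (YPT), 300 per group at 8 months, one-tailed alpha 0.05, planned power 0.80. Not in the article and therefore assumed: a share f already in LDKT Action at baseline, taken as 10% to 40%.

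**Formula.** Power for two proportions with n per group: Φ[(d − z·se0)/se1], where d = p2 − p1, se0 = √(2·p̄(1−p̄)/n) with p̄ the mean of p1 and p2, se1 = √((p1(1−p1)+p2(1−p2))/n), and z = 1.645 one-sided or 1.960 two-sided.

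**The plan's own figure.** The article says: "Assuming a one-tailed alpha of 0.05, a sample size of 300 patients per group is required at 8 months post-baseline to achieve power of 0.80". The standard formula for 10% versus 20% at 80% power gives 157 per group one-sided (177 with continuity correction) and 199 two-sided (219 with correction). With 300 per group, power is 0.964 one-sided and 0.931 two-sided. So 300 is not reproduced. That is a separate matter, but it means the design carries a surplus.

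**Three readings**, each with 10% versus 20% moving among patients not in Action at baseline:

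- A. Moving into Action, at-risk patients only: n = 300(1−f), 10% versus 20%.
- B. Moving into Action, everyone in the denominator and baseline-Action patients as non-movers: n = 300, 0.1(1−f) versus 0.2(1−f).
- C. In Action at 8 months, unadjusted, with nobody leaving Action: n = 300, f+0.1(1−f) versus f+0.2(1−f).

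**Worked at f = 20%.**

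- A: n = 240, p̄ = 0.15, se0 = 0.0326, se1 = 0.0323. (0.10 − 1.645×0.0326)/0.0323 = 1.44, power 0.92.
- C: 28% versus 36%, p̄ = 0.32, se0 = 0.0381, se1 = 0.0379. (0.08 − 1.645×0.0381)/0.0379 = 0.46, power 0.68.

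**Power, one-sided / two-sided:**

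| Baseline share f | A: at risk only | B: counted as non-movers | C: status, unadjusted |
|---|---|---|---|
| 0% | 0.96 / 0.93 | 0.96 / 0.93 | 0.96 / 0.93 |
| 10% | 0.95 / 0.90 | 0.94 / 0.90 | 0.83 / 0.74 |
| 20% | 0.92 / 0.87 | 0.92 / 0.86 | 0.68 / 0.56 |
| 30% | 0.89 / 0.82 | 0.88 / 0.80 | 0.54 / 0.42 |
| 40% | 0.85 / 0.76 | 0.82 / 0.73 | 0.43 / 0.31 |

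Under B the 10-point difference becomes 9, 8, 7 and 6 points at f = 10% to 40%. Under C the difference is the same, but it sits on a higher and more variable base rate.

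**A fourth reading.** If 10% and 20% are themselves the status rates at 8 months, power at 300 per group is 0.964 one-sided and 0.931 two-sided, with no loss. If nobody leaves Action, a 10% UC status rate also caps the baseline share at 10%.

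**The case against.** The strongest reply is that the text nearly settles the matter. Three of the four wordings describe a transition, only the opening of the power section describes a status, and that section ends on moving to Action. This largely stands: transition is the more natural reading, and under it the planned one-sided power is kept throughout the assumed range. It does not settle how baseline-Action patients are counted, which separates readings A and B.

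Four stronger readings are tempting, and the documents do not support them.

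- A reader might infer that the trial loses most of its power. Column C produces that only by treating 10% and 20% as transition rates, analysing status without adjustment, assuming that nobody leaves Action, and supplying a baseline share. The article states none of these as a combination.
- A reader might infer that many patients start in Action because all have booked a transplant evaluation. The article's scale makes undergoing evaluation the DDKT Action stage. LDKT Action is defined separately, so the booking says little about it.
- A reader might treat the unnamed baseline covariate as an error. A journal article commonly leaves covariates to the full protocol or analysis plan. Under randomization, not adjusting costs precision and leaves chance imbalance in place; it does not bias the comparison.
- A reader might object that dropping baseline-Action patients leaves fewer than 300 per group. That is true, but 10% versus 20% needs only 157 one-sided or 199 two-sided.

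**Conclusion.** The inconsistency is real and limited. The sizing outcome is described both as a status and as a transition, the planned analysis uses the transition, and the place of baseline-Action patients in numerator and denominator is not fixed.

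Under the transition wording the consequence is modest. One-sided power at 300 per group is 0.95 to 0.85 (at risk only) or 0.94 to about 0.82 (counted as non-movers) for baseline shares of 10% to 40%. Tested two-sided, both fall below 0.80 at a 40% share (0.76 and 0.73). A serious loss, to about 0.68 at 20% and 0.54 at 30% one-sided, arises only under the unadjusted status comparison and its added assumptions. All the shares are assumptions.

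This is a worthwhile, inexpensive clarification and gain in precision, not an error that invalidates the plan.

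**What to change.** 1. Use one definition of the 8-month outcome in both the power section and the statistical analyses section.
2. State how patients in LDKT Action at baseline enter the numerator and the denominator.
3. State whether 10% and 20% are status rates or transition rates.
4. Include baseline LDKT stage as a covariate in the planned 8-month logistic regression. If only at-risk patients are analysed, adjust for the remaining stages. If baseline-Action patients are kept and all share one outcome, that level is separated in the logistic model and adds no information on the treatment effect, so say how this will be handled.

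If the transition outcome is kept, the cost is wording plus one covariate already collected in both arms. If a status outcome is chosen and 10% and 20% were meant as transition rates, wording alone is not enough: the expected rates and the power must be restated. Either way, make the choice before outcome data are examined by arm.

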### YPT baseline education and coaching

Typically within 14 days post-baseline survey, patients randomized to YPT will have a separate 25-minute baseline coaching telephone call. During this call, as prompted by bulleted coaching recommendations generated by the YPT computerized program, the coach will discuss the most relevant content to support each patient in completing transplant evaluation successfully and pursuing LDKT. Immediately after the call, the coach will mail each patient a folder containing the informed consent documents, an individually-tailored feedback report generated from their answers to the baseline survey, print DDKT and LDKT educational resources, including a *Community Resource Guide*, and a $10 gift card.

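### The knowledge, self-efficacy and decisional-balance comparisons count baseline as an occasion and state no baseline adjustment; read in the usual way, this costs about 10-22% of the information

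*Protocol article*

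**What the plan says.** All references are to the protocol article.

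- **Comparison.** Under Statistical analyses, for knowledge and for DDKT/LDKT self-efficacy and decisional balance: "comparisons between the YPT and UC conditions by these three occasions will be made to determine if the intervention increases transplant knowledge".
- **Occasions.** They are defined one sentence earlier, for readiness: "change by three occasions (baseline, 4 months post-baseline, and 8 months post-baseline) will be examined". The knowledge comparison by race later in the section uses the same three.
- **Model.** "random effects models will be used to account for longitudinal measurement and linear regression employed for normally distributed outcomes".
- **Missing data.** "Multiple imputation of missing data will be used for the analyses".
- **Timing of baseline.** Under YPT baseline education and coaching: "Typically within 14 days post-baseline survey, patients randomized to YPT will have a separate 25-minute baseline coaching telephone call". The baseline survey therefore cannot reflect the intervention.
- **Covariates.** Race and the barrier variables are named as model terms. The patient's baseline score on the scale being analysed is not.
- **Contrast.** The text does not say which contrast is tested, or whether baseline means are free or held equal between arms.

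**The concern.** The arms are compared on an occasion that the intervention could not have affected, and nothing says that baseline is used to explain variation in the later scores. An analyst following this wording would most naturally fit arm, occasion and their interaction, with a separate baseline mean per arm. The interaction at 8 months is then the difference between arms in change from baseline. That contrast subtracts the whole baseline score, although only a fraction of it predicts the later score, and so it carries avoidable noise.

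Transplant knowledge is one of the trial's stated aims, but the Power and sample size section covers only the proportion in the Action stage. The scales have no precision target of their own, so an avoidable loss could hide a modest YPT effect. The comparisons by race rest on smaller groups, where lost precision matters more.

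**Working it through.** **The plan's own figure.** There is none for these scales: no SD, correlation or power is given. The 300 per group in Power and sample size belongs to the Action-stage proportion. It is used below only as the planned number followed.

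**Inputs**

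- 450 per arm at baseline and 300 per arm at 8 months (Power and sample size).
- Correlation r between baseline and 8-month scores: not in the article. Assumed range 0.4-0.7.
- Equal SDs at both surveys, scaled to 1, and a linear model (assumed). The small-steps counts would use Poisson regression and are not covered by these formulas.

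**Step 1: variance of the 8-month effect**

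(a) Change from baseline, 300 complete cases per arm: 2(1-r) x 2/300.

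(b) Change from baseline in a free-means mixed model with 450 baselines and 300 follow-ups. Per arm, the estimate is (8-month mean - r x baseline mean, both in the 300) - (1-r) x (baseline mean in the 450). The two parts are independent, so the variance of the arm difference is 2 x [(1-r^2)/300 + (1-r)^2/450].

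(c) Adjusted for baseline: (1-r^2) x 2/300. A three-occasion model with a common baseline mean gives the same, because the shared mean cancels from the arm difference.

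**Step 2: information kept by the change contrast**

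The ratio c/a is (1-r^2)/[2(1-r)] = (1+r)/2.

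| r | SE (a) | SE (b) | SE (c) | c/a | c/b | loss, complete cases | loss, 450/300 |
|---|---|---|---|---|---|---|---|
| 0.4 | 0.0894 | 0.0849 | 0.0748 | 0.70 | 0.78 | 30% | 22.2% |
| 0.5 | 0.0816 | 0.0782 | 0.0707 | 0.75 | 0.82 | 25% | 18.2% |
| 0.6 | 0.0730 | 0.0706 | 0.0653 | 0.80 | 0.86 | 20% | 14.3% |
| 0.7 | 0.0632 | 0.0616 | 0.0583 | 0.85 | 0.90 | 15% | 10.5% |

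Example for (b) at r = 0.5: 2 x (0.75/300 + 0.25/450) = 2 x (0.002500 + 0.000556) = 0.00611, so SE = 0.0782. For (c): 0.75 x 2/300 = 0.00500, so SE = 0.0707. The ratio is 0.00500/0.00611 = 0.82.

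**Step 3: check with the 4-month survey in the model.** A generalised least squares calculation used three equally correlated occasions, with 75 of the 150 drop-outs per arm still seen at 4 months (assumed). The losses are 22.5%, 18.5%, 14.6% and 10.9% for r = 0.4 to 0.7. With complete data they are exactly 30%, 25%, 20% and 15%.

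**Step 4: what this does to power.** Two-sided 0.05, r = 0.5, effect sizes assumed. Power is the normal probability below (effect/SE - 1.96).

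- 0.2 SD: 0.2/0.0782 - 1.96 = 0.60, power 72%, against 0.2/0.0707 - 1.96 = 0.87, power 81%. With complete cases only, the change contrast has 69%.
- 0.3 SD: 0.3/0.0782 - 1.96 = 1.88, power 97%, against 0.3/0.0707 - 1.96 = 2.28, power 99%.

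**The case against.** The strongest objection is that the article does not fix the model. Having baseline among the outcome occasions does not by itself cause the loss: with a common baseline mean the same three occasions lose nothing, and the article does not exclude that model. The parameterisation may sit in an analysis plan that is not shown. This stands to the extent that a reader might infer that the plan commits itself to change scores; it does not. What remains is that the text names the occasions for comparison, includes a pre-intervention one and states no baseline adjustment, so the natural reading leads to the less efficient contrast.

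Other stronger readings also go beyond the text:

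- **A 30% loss.** That needs r = 0.4 and a complete-case analysis, whereas random effects models and multiple imputation are planned.
- **A test diluted over two degrees of freedom.** No joint test across visits is stated.
- **Every patient-reported comparison is affected.** The decisional-conflict and informed-decision ratings are collected at the final assessment and have no baseline occasion.
- **Biased or over-corrected estimates.** Under randomisation both contrasts are unbiased.

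A further fair point is that, under Patient recruitment, eligibility, randomization, and retention, records are randomised before patients are invited and consent. Baseline means among consenters may therefore differ by more than chance. Neither change scores nor adjustment would fully repair such selection. It does, however, argue against a model that asserts equal baseline means.

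**Conclusion.** The point holds as a loss of precision under the usual reading of the text. With the planned 450 baselines and 300 follow-ups per arm and r of 0.4-0.7, the change contrast gives up about 10-22% of the information that a baseline-adjusted comparison would use. The complete-case figure is 15-30%. At r = 0.8, outside the assumed range, the 450/300 loss falls to about 7%: (1-r^2)/300 = 0.00120 against 0.00120 + 0.04/450 = 0.00129.

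The correlation and the effect sizes are assumptions. The effect on power is noticeable near 0.2 SD (72% against 81% at r = 0.5) and slight at 0.3 SD. The scales concerned carry no power claim. This is an inexpensive improvement and does not threaten the trial's validity.

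**What to change.** Under Statistical analyses, state that for knowledge, self-efficacy and decisional balance:

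1. the 4- and 8-month scores are the outcomes in the random effects model;
2. the patient's own baseline score, and its interaction with visit, are covariates;
3. the YPT effect is the arm difference at 8 months, with 4 months secondary.

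Use the same form for the knowledge comparison by race. A three-occasion model with a common baseline mean would be equally efficient. Because allocation precedes consent, the covariate form is the safer choice: it conditions on the scores observed and does not assert equal baseline means among consenters.

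The cost is a change of wording. The baseline survey is already collected in both arms, patients with a baseline and any follow-up contribute, and the planned multiple imputation covers the rest.

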### Predictors and covariates

#### Demographic, clinical and cultural factors

Many other patient characteristics will be assessed including age, sex, race/ethnicity, dialysis status (on or off dialysis; if on, hemodialysis or peritoneal), patient comorbidities (e.g., the presence of diabetes, hypertension, polycystic kidney disease) and validated measures of health-related quality of life, including the Medical Outcomes Study (MOS) SF-12v2 [48] and a patient-reported Karnofsky rating of health status [49]. To examine how other known causes for health disparities in transplant affect key outcomes we will also assess medical mistrust using the Medical Mistrust Index, a validated scale that assesses patients’ agreement with 7-items about their trust of health care organizations (E.g., “Patients have sometimes been deceived or misled by health care organizations”) [29, 50].

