#### Social support and availability of living donors

Social support will be assessed by examining discordance on responses to two items measured on a 4-point Likert scale ranging from “None” to “A great deal”: “In the past 6 months, how much help or support have you received, related to your kidney disease?”; “In the past 6 months, how much help or support have you needed, related to your kidney disease?” [52]. Availability of donors will be assessed by measuring the number of close and extended family members and friends a patient has, presence of kidney disease or other comorbidities (e.g., diabetes and hypertension) in these groups, and the number of donor offers.

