To determine whether, compared to the UC group, Black, Hispanic and White patients receiving YPT are more likely to complete transplant medical evaluation and pursue LDKT 18-months post-baseline, regression models will be fit with: 1) only the treatment condition as a predictor; 2) race added-in as a covariate; 3) an interaction term between treatment and race. To examine whether the YPT’s effectiveness in changing LDKT decision-making and behavior is different between Blacks, Hispanics and Whites, comparisons will be made of proportional forward movement in readiness at 8 months post-baseline between Black, Hispanic and White patients in the YPT condition. Also, Black, Hispanic and White patients will be compared on three occasions (baseline, 4 months post-baseline, and 8 months post-baseline) to determine if access to YPT increases transplant knowledge differently for Black, Hispanic and White patients through this follow-up period and if the intervention has different effectiveness on the increase in proportion of living donors being evaluated for LDKT and increases in the proportion of LDKTs among Black, Hispanic and White patients 18-months post-baseline.

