Finally, to examine how known patient, family, and healthcare system barriers to LDKT act alone and in combination with YPT to affect Black and Hispanic patients’ decision-making and behavior around LDKT, the direct effects of key modifiable and non-modifiable variables known to affect disparities in receipt of LDKT (e.g., medical mistrust, quality of health insurance, physician recommendation to pursue LDKT) on readiness to pursue LDKT, transplant knowledge, completion of transplant evaluation, and receipt of LDKT will be adjusted for in regression models of YPT’s effect on these outcomes for Blacks and Hispanics separately. Then, interactions between YPT and these factors will be added to the models. Specifically, we will model each dependent variable first using the main effects of the barrier variables and of the YPT intervention, and then add two-way interactions between the intervention and the barrier variables. Similar models will be constructed for White patients. Based on these models, we will determine: (1) the estimated magnitude of racial differences between Black, Hispanic and White patients with and without access to the YPT for each outcome, and (2) which patient and care-related variables represent important confounding and modifying effects for explaining racial/ethnic differences in each outcome. These analyses will help elucidate whether the YPT achieves results by attenuating the impact of specific ‘causes’ of racial/ethnic disparities in LDKT.

Qualitative analyses will be performed to understand responses to key open-ended questions asked in the survey, particularly those around socioeconomic barriers to patients’ pursuit of transplant, potential solutions to barriers patients face in their transplant pursuit, and actions patients are willing to take toward LDKT and DDKT. Patients’ responses will be coded and analyzed to determine themes.

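### The pooled 18-month models adjust for race at most and so give up some precision that baseline values likely to be prognostic could supply

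*Protocol article*

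**What the plan says.** The Statistical analyses section sets out the overall YPT versus usual care (UC) comparison of the two 18-month outcomes as a sequence: "regression models will be fit with: 1) only the treatment condition as a predictor; 2) race added-in as a covariate"; then "3) an interaction term between treatment and race". Nothing else is placed in these pooled models.

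The same section later plans a second family of models. Barrier variables ("e.g., medical mistrust, quality of health insurance, physician recommendation to pursue LDKT") have direct effects "on readiness to pursue LDKT, transplant knowledge, completion of transplant evaluation, and receipt of LDKT", and these "will be adjusted for in regression models of" YPT's effect "on these outcomes for Blacks and Hispanics separately", with similar models for White patients. Treatment-by-barrier interactions follow. The stated purpose is to explain racial and ethnic differences.

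Under Predictors and covariates, the article lists "dialysis status (on or off dialysis; if on, hemodialysis or peritoneal") among the patient characteristics. Donor availability is measured by family and friends, their illnesses "and the number of donor offers". Survey timepoints places LDKT readiness and clinical characteristics in the baseline assessment, and Outcome measures gives LDKT readiness four stages.

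**The concern.** How far a patient has already gone towards LDKT at enrolment probably predicts whether a transplant follows within 18 months. The eligibility criteria do not exclude patients who already have a donor offer, and the article describes no stratification by donor offer. A pooled model with treatment and race alone leaves that variation in the error.

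The covariate set for these models is stated, not left open, so this is a choice in the plan and not detail deferred to another document. Power and sample size addresses only the 8-month Action-stage outcome, so the 18-month comparisons have no stated margin of power to spare. What is at stake is the precision of the YPT estimate for the two record-based outcomes.

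**Working it through.** **The plan's own figure.** There is none for the 18-month outcomes. The 300 per group in Power and sample size belongs to the 8-month Action-stage comparison and is not used here. (It does not follow from its own inputs: 10% versus 20%, one-tailed 0.05 and power 0.80 give 157 per group. That is a separate matter.)

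**Inputs from the article.** 450 patients per group, equal allocation; 18-month outcomes from medical records for both groups, so all 900 are taken as analysed; alpha 0.05. The analysis section does not state sidedness; two-sided is assumed.

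**Inputs assumed.** All outcome rates, covariate frequencies and predictor strengths.

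**Check 1: moderate to strong predictors.** Two binary baseline covariates: any donor offer (40% of patients) and on dialysis (70%). Logistic models, Wald test of treatment, 3,000 simulated trials per cell. Monte Carlo standard error of each power is about √(0.77 × 0.23 / 3000) = 0.8 points. Cells show power without → with the two covariates.

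| Outcome, UC vs YPT | Odds ratios 2 and 0.67 | 4 and 0.5 | 8 and 0.4 |
|---|---|---|---|
| 5% vs 9% | 0.65 → 0.65 | 0.67 → 0.68 | 0.65 → 0.68 |
| 10% vs 16% | 0.77 → 0.77 | 0.77 → 0.80 | 0.77 → 0.82 |
| 50% vs 59% | 0.77 → 0.79 | 0.77 → 0.82 | 0.77 → 0.86 |

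The gain is about 0 to 5 points in the first two rows, which resemble LDKT, and about 2 to 10 in the third, which stands for completed evaluation. With no treatment effect (10% in both arms, odds ratios 4 and 0.5) the rejection rate is 5.1% unadjusted and 5.2% adjusted.

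**Check 2: donor offer as a very strong predictor.** Donor offer alone is adjusted for, with a YPT odds ratio of 2.0 and 2,000 simulated trials per scenario.

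| Have an offer | LDKT in UC, offer vs none | Unadjusted → adjusted |
|---|---|---|
| 30% | 20% vs 3% | 0.83 → 0.87 |
| 30% | 30% vs 3% | 0.83 → 0.89 |
| 30% | 40% vs 3% | 0.81 → 0.91 |
| 20% | 25% vs 4% | 0.82 → 0.87 |

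In the 3% rows the donor-offer odds ratio runs from (0.20/0.80)/(0.03/0.97) = 8.1 to (0.40/0.60)/(0.03/0.97) = 21.6. A gain of 10 points needs the upper end.

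**Check 3: chance imbalance.** With 30% holding an offer, the between-arm difference in that share has SD √(2 × 0.3 × 0.7 / 450) = 3.06 points, and 1.96 SD is 6.0 points. The LDKT difference then shifts by 6.0 × (0.20 − 0.03) = 1.0 to 6.0 × (0.40 − 0.03) = 2.2 points.

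For comparison, in the 20% vs 3% scenario UC has 0.3 × 0.20 + 0.7 × 0.03 = 8.1%. An odds ratio of 2.0 turns 20% into 33.3% and 3% into 5.8%, so YPT has 0.3 × 0.333 + 0.7 × 0.058 = 14.1%, a difference of 6.0 points. The unadjusted 95% half-width is 1.96 × √[(0.081 × 0.919 + 0.141 × 0.859)/450] = 4.1 points. The shift of 1.0 point in this scenario lies well inside it.

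**Check 4: which effect is estimated.** At 10% vs 16% the unadjusted odds ratio is (0.16/0.84)/(0.10/0.90) = 1.71. In the strongest-covariate cell of Check 1 the conditional log odds ratio is 0.616, an odds ratio of 1.85. The two differ by non-collapsibility even with perfect balance, so the reported effect measure needs naming.

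**Check 5: room for covariates.** Treatment (1), race (2), LDKT stage as one term (1), dialysis (1) and donor offer (1) make 6 terms; stage at all four levels makes 8. Assumed LDKT rates of 5% vs 9% give 450 × 0.05 + 450 × 0.09 = 63 events, and 10% vs 16% give 117.

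**The case against.** **The planned analysis is valid.** Treatment alone, then race, then the interaction is a legitimate analysis of a randomised trial, and its error rate is right. This stands: the point is about efficiency.

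**Adjustment is already planned.** A reader might infer from the pooled sequence that the whole plan uses only treatment and race. It does not: the barrier models cover both 18-month outcomes, and their covariates are given only as examples. But they are fitted within each race group to explain disparities, and yield no pooled adjusted YPT effect.

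**Imbalance.** A reader might infer that chance imbalance in donor offers biases the YPT effect. It does not. A 1.96 SD imbalance is a one-in-twenty extreme that the unadjusted standard error already allows for; it moves the single realised estimate. Recruitment has records randomised before patients are contacted, so consenting arms could differ for reasons other than chance. That is a different issue, which adjustment would repair only in part.

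**Timing of donor offers.** No time point is given for them. The baseline content listed under Survey timepoints does not name them, and Data management has social support, the heading they share, captured at baseline, 4 and 8 months. YPT teaches patients how to find donors, so a later count is affected by treatment and must not be adjusted for. This stands and limits the fix.

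**Strength and importance.** Nothing in the article shows how strongly donor offers or dialysis status predict the outcomes; likely prognostic is as far as one can go. Nor does it make LDKT receipt the outcome on which the trial is powered; that is 8-month readiness.

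**Conclusion.** The point holds as a modest, nearly free improvement. The pooled 18-month YPT versus UC models adjust for race at most, and no pooled estimate uses the likely prognostic values that the trial collects.

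The gain is about 0 to 5 power points for an uncommon outcome such as LDKT, up to about 10 only if donor offer is a very strong predictor, and about 2 to 10 for a common one such as completed evaluation. With moderate predictors and a rare outcome it is nil. These figures rest on assumed rates and predictor strengths and on the Wald test of the odds ratio; the test on a standardised risk difference was not simulated.

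The documents do not support calling the planned comparison biased or invalid, or its error rate inflated. The 8-month readiness outcome is outside this point.

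**What to change.** For each 18-month outcome, name one main pooled model containing:

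- treatment;
- race;
- baseline LDKT stage, as Action versus not or as a single ordinal term;
- dialysis status, on versus off;
- any living-donor offer, yes or no, recorded in the baseline survey before the first coaching contact, and never a later count.

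If donor offers are not asked at that point, leave the term out or add the item to the baseline survey. Report the YPT effect as a risk difference standardised over the trial population, with its confidence interval. Keep the treatment-only model as supportive, and use the interaction model only for the race question. This also settles which of the three sequential models gives the overall result.

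The cost is a few lines in the analysis section and, if donor offers are already asked at baseline, no new data. Some baseline items may be missing, which the planned multiple imputation can handle. The list should stay at about these six terms, or fewer if LDKT events prove scarce.
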